# Protocol of the Italian Radical Cystectomy Registry (RIC): a non-randomized, 24-month, multicenter study comparing robotic-assisted, laparoscopic, and open surgery for radical cystectomy in bladder cancer

**DOI:** 10.1186/s12885-020-07748-7

**Published:** 2021-01-11

**Keywords:** Cancer, Neoplasm; bladder, Urinary, Robotic, Surgery, Bladder reconstruction, Prostate

## Abstract

**Background:**

Bladder cancer is the ninth most common type of cancer worldwide. In the past, radical cystectomy via open surgery has been considered the gold-standard treatment for muscle invasive bladder cancer. However, in recent years there has been a progressive increase in the use of robot-assisted laparoscopic radical cystectomy. The aim of the current project is to investigate the surgical, oncological, and functional outcomes of patients with bladder cancer who undergo radical cystectomy comparing three different surgical techniques (robotic-assisted, laparoscopic, and open surgery). Pre-, peri- and post-operative factors will be examined, and participants will be followed for a period of up to 24 months to identify risks of mortality, oncological outcomes, hospital readmission, sexual performance, and continence.

**Methods:**

We describe a protocol for an observational, prospective, multicenter, cohort study to assess patients affected by bladder neoplasms undergoing radical cystectomy and urinary diversion. The Italian Radical Cystectomy Registry is an electronic registry to prospectively collect the data of patients undergoing radical cystectomy conducted with any technique (open, laparoscopic, robotic-assisted). Twenty-eight urology departments across Italy will provide data for the study, with the recruitment phase between 1st January 2017-31st October 2020. Information is collected from the patients at the moment of surgical intervention and during follow-up (3, 6, 12, and 24 months after radical cystectomy). Peri-operative variables include surgery time, type of urinary diversion, conversion to open surgery, bleeding, nerve sparing and lymphadenectomy. Follow-up data collection includes histological information (e.g., post-op staging, grading, and tumor histology), short- and long-term outcomes (e.g., mortality, post-op complications, hospital readmission, sexual potency, continence etc).

**Discussion:**

The current protocol aims to contribute additional data to the field concerning the short- and long-term outcomes of three different radical cystectomy surgical techniques for patients with bladder cancer, including open, laparoscopic, and robot-assisted. This is a comparative-effectiveness trial that takes into account a complex range of factors and decision making by both physicians and patients that affect their choice of surgical technique.

**Trial registration:**

ClinicalTrials.gov, NCT04228198. Registered 14th January 2020- Retrospectively registered.

## Background

### Epidemiology of bladder cancer

Bladder cancer is the ninth most common type of cancer worldwide, with 75% of the total burden occurring in men [1]. In Europe the age-standardized incidence rate is 19.1 for men and 4.0 for women, and mortality rates (per 100,000 persons years) are 3.2 for men and 0.9 for women [2]. Bladder cancer increases with age and, although it is higher in men than women [1], incidence in both sexes is expected to increase in European countries [3]. Cigarette smoking has been identified as one of the main risk factors for bladder cancer [3, 4], and incidence rates are higher in more developed countries [5].

At initial diagnosis, cancer neoplasms present as a non-muscle-invasive pathology in 70–75% of cases, and a muscle-invasive form in about a quarter of cases [6]. In about one third of patients with a diagnosis of muscle-invasive bladder tumor, the neoplasm is found to be a metastasis that was not identified during treatment of the primary tumor; in particular, lymph node involvement is identified during surgery in about 25% of patients receiving a radical cystectomy [7].

### Radical cystectomy: the gold standard

Since the 1960s, treatment with radical cystectomy has been the gold standard for invasive tumors of the bladder wall and is indicated for non-muscle-invasive bladder neoplasms with a high risk of progression or relapse that are non-responsive to intra-bladder immunotherapy (intravesical instillation of Bacillus Calmette-Guerin (BCG)), and in cases of pelvic neoplasms infiltrating the bladder [7–9]. In urology, cystectomy is considered to be one of the most technically challenging oncological interventions. Radical cystectomy involves removal of the entire bladder and lymph node dissection. In men, the prostate is often removed as well as the seminal vesicles, while in women the uterus, ovaries, and a small portion of the vagina and fallopian tubes are removed. Surgery includes the removal phase, followed by a reconstruction phase, which may consist of incontinent (using an ileal conduit) or continent (using a urethral or cutaneous neobladder) urinary diversion. The type of urinary diversion chosen varies according to the cancer stage and grade, prognosis, comorbidity, and functional status of the patient as well as potential contraindications to creating a neobladder [10, 11]. There are many factors that can be used to evaluate the success of treatment, including peri-operative outcomes (such as blood loss, mortality, hospital stay, complication rates etc), and short- or long-term outcomes (including overall survival, recurrence-free survival, and cancer-specific survival), as well as functional outcomes (such as continence and sexual potency).

### New, minimally invasive approaches and treatments: robot-assisted laparoscopic radical cystectomy

In the past, radical cystectomy via open surgery has been considered the gold-standard treatment for muscle invasive bladder cancer. However, in recent years there has been a progressive increase in the use of robot-assisted laparoscopic radical cystectomy [12], which is a challenging procedure suitable for both older and younger patients [13, 14] that can be improved with specific training and a skilled robotic team [15]. A recent review suggested that there are several advantages to the robot-assisted technique, such as lower blood loss and transfusion rate during surgery, and possibly faster gastrointestinal recovery, and a shorter length of hospital stay [16]. Studies have mostly found that peri-operative and short-term outcomes are similar when using robot-assisted versus open radical cystectomy [17–20], but some data suggests that assisted radical cystectomy improves minor, but not major, complications compared to open surgery [9], especially in terms of lower blood loss and shorter time to returning to a regular diet [17, 21, 22]. Few data on long-term oncological outcomes are available; initial studies report comparable outcomes for robot-assisted versus open radical cystectomy [19, 22–28]. Data on the long-term functioning of patients is also sparse, with no studies directly comparing urinary continence or sexual potency in patients receiving robot-assisted versus open radical cystectomy [16]. Robot-assisted radical cystectomy has been reported to cost more than open surgery due to higher supply costs [12], although to accurately assess the economic advantages of each technique, long-term studies that assess cancer recurrence, readmission rate, rehospitalization, and other health economic variables are needed.

### Need for large scale, multicenter registries

There are currently very few Randomized Control Trials (RCT) comparing robot-assisted laparoscopic versus open radical cystectomy [17], and previous non-randomized studies are hampered by small sample sizes and short follow-ups. Although RCTs are the preferred study design for evaluating treatment efficacy there is also a need for comparison-effective studies, because there are multiple factors that determine the choice and outcomes of surgical techniques in real-life clinical settings, including complex clinical decision making, patient and hospital characteristics, and surgical expertise. The current study aims to provide data to this rapidly developing field by creating a nationwide, multicenter registry with two-year post-surgery follow-up of bladder cancer patients who will undergo bladder cystectomy, with a comprehensive data collection on multiple outcomes.

## Aims

The aim of the project is to investigate the surgical, oncological, and functional outcomes of patients with bladder cancer who undergo radical cystectomy comparing three different surgical techniques (robotic-assisted, laparoscopic, and open surgery). Pre-, peri- and post-operative factors will be examined, and participants will be followed for a period of up to 24 months to identify risks of mortality, oncological outcomes, hospital readmission, sexual performance, and continence.

## Methods & design

### Study design and setting

This article describes the Italian Radical Cystectomy Registry - “Registro Italiano Cistectomia Radicale (RIC)”. The trial has been retrospectively registered on ClinicalTrials.gov on 14/01/2020 with reference number NCT04228198. The study is an observational, prospective, multicenter, cohort study to assess patients affected by bladder neoplasms undergoing radical cystectomy and urinary diversion. This protocol was developed in accordance with the Standard Protocol Items: Recommendations for Interventional Trials (SPIRIT) Statement. Twenty-eight participating centers across Italy will provide data for the study. All centers have a similar peri-operative pathway; all use enhanced recovery after surgery (ERAS) protocols. The centers are: Urology Clinic, University of Bologna; Department of Urology, AOU Careggi, Florence; European Institute of Oncology Milan; San Raffaele Hospital, Milan; University Hospital of Verona; Department of Urology, Policlinico Abano; Department of Urology, Spedali Civili, Brescia; Department of Urology and Kidney Transplantation, University of Foggia, Foggia; Galliera Hospital, Genova; ASST Niguarda Metropolitan Hospital, Niguarda; Policlinico Umberto I, Saproma; Department of Clinical Urology, University of Perugia; Department of Clinical Urology, AOUP Cisanello Hospital, Pisa; Department of Clinical Urology, Palermo University, Palermo; Department of Clinical Urology, Alessandria Hospital, Alessandria; Department of Clinical Urology, ASST Mantova, Mantova; Department of Clinical Urology, ASL Abruzzo; Department of Clinical Urology Ca Foncello Hospital, Treviso; Department of Clinical Urology II, Bari University, Bari; Department of Clinical Urology, Vittorio Emanuele Hospital, Catania; Department of Clinical Urology, Casa Sollievo della Sofferenza, Sgrotondo; Hospital Bassiano, Bassano; Department of Clinical Urology, Hospital San Francesco ASL 3, Nuoro; Department of Clinical Urology*,* Portogruaro; Department of Clinical Urology, Biella Hospital, Biella; Department of Clinical Urology Chioggia Hospital; Ausl Modena; Department of Urology and Kidney Transplantation, Bianchi-Melacrino-Morelli Grand Metropolitan Hospital.

### Participants

We will include patients with a histologically confirmed diagnosis of bladder cancer between January 1st 2017 and October 31st 2020, who will be treated in the participating medical centers. Eligibility screening will be conducted by the examining physician according to the following inclusion criteria: 1) male and female consecutively recruited patients; 2) age ≥ 18 years; 3) histologically confirmed diagnosis of bladder cancer eligible for radical cystectomy (according to EAU guidelines [7]) at date of enrollment; 4) providing written, informed consent. We aim to enroll approximately 1000 patients in the baseline data collection.

### Ethical issues

Data collection will be conducted in accordance with the *World Medical Association Declaration of Helsinki*. All potential participants will be required to sign an Informed Consent form. Ethical permission was received from the Ethical Committee of the University of Padova (number: 0042389). The standard of care will remain unchanged in patients participating in this study.

### Database design and management

The Italian Radical Cystectomy Registry is an electronic registry to prospectively collect the data of patients undergoing radical cystectomy conducted with any technique (open, laparoscopic, robotic-assisted), similar to one used by an International consortium. The protocol was designed by a Scientific Committee of Italian experts, who regularly reviews the database and proposes any relevant changes and integrations that may be useful for fulfilling the project aims. The database is based on an online platform. Information from patients will be collected in a confidential manner, according to Italian privacy Laws (Decreto Legislativo 196/2003); each patient will be identified via an anonymous identification code. Data will be used in an aggregated form. Each individual center will be responsible for the personal data collected in relation to the project. The information collected will be registered by the responsible physician in each center on the internet-based data storage file, which is accessible via username and password. The data will be regularly transferred to a global database. The data will be checked and cleaned by an Epidemiologist and any data inconsistencies or missing values will be directly resolved with the individual centers. All data will be analyzed anonymously. The Steering Committee will grant access for data analysis to individual researchers according to requests from the participating centers.

### Data collection

Figure 1 illustrates the three phases of the study, and some of the key data that will be collected.

**Fig. 1 Fig1:**
[figure not shown]
Study phases and summary of key data

#### Phase I: recruitment of participating centers

All clinics and hospitals in Italy that currently carry out radical cystectomy with all three surgical techniques were contacted to establish interest in participating in the study. Participation is on a voluntary basis, and the centers will receive no additional funding for participating. A responsible physician in each participating center will be assigned the role of managing the data collection, guaranteeing the systematic recruitment of eligible patients, and supervising collection and coding of data according to the web-based data collection form. The questions used in the data collection form were designed by the Scientific and Steering Committee and include pre-specified categories for some questions and open fields for others, where appropriate. Shortly after the first date of patient recruitment the Scientific Committee reviewed a selection of the inputted patient data at each clinic to ensure homogeneity of reporting and modify any database issues.

#### Phase II: enrollment of patients

Urology departments of the participating centers will identify eligible patients during the recruitment phase (1st January 2017-31st October 2020) in accordance with the inclusion criteria. All potential participants will be given an informative letter explaining details of the study and will be asked to sign an informed consent form. After written, informed consent is provided information will be collected from the patients at the moment of surgical intervention and during follow-up (3, 6, 12, and 24 months after radical cystectomy). Surgical technique will not be randomized and will be assigned according to the clinical judgement of the surgeon. All participants will undergo usual clinical care.

#### Phase III: follow up

After 3, 6, 12, and 24 months post-surgery, data will be taken directly from the patients at their follow-up medical visits and entered into the online database. The physician identifying and recruiting patients will oversee the completion of the data collection forms during follow-up, even if the patient is subsequently treated in another center.

### Variables

Data will be collected by the medical team during the patient’s hospital admission and at clinical visits during the follow-up. Variables of interest include demographic variables (age, sex, etc), surgical factors (technique use, length of surgery, blood loss, type of urinary diversion, node burden, histological exams, surgical margins etc), mortality, morbidity (pre-, during- and post-surgery), oncological results, and functioning (continence and sexual performance) over follow-up, as detailed below. All health and biological data will be taken in accordance with usual clinical care of the patients and will be stored at the participating centers in accordance with national laws and guidelines.
**Patient data** includes sex, date of birth, and body mass index.**Pre-operatory data** includes the name of the surgeon, date of operation, and American Society Anesthesiologists (ASA) physical status classification system [29]. During the physician’s examination information from the patient’s medical records and the physical examination will be used to identify comorbid medical conditions (diabetes, hypertension, cardiopathy, chronic obstructive pulmonary disease, ransient ischemic attack, anticoagulant-antiplatelet therapy, and other pathologies). The Charlson comorbidity score will be calculated [29]. Preoperative grading and staging of the bladder neoplasm will be done according to standard criteria (EAU) including T-stage, G-stage, and presence of a concomitant carcinoma in situ (CIS). Preoperative therapeutic interventions, including neoadjuvant chemotherapy, palliative cystectomy, and BCG-instillation will be recorded.**Peri-operative data.** Data on the surgical procedure will be categorized according to the technique used for cystectomy (open / robotic-assisted / laparoscopic) as well as for urinary diversion (open / robotic-assisted / laparoscopic). Type of urinary diversion (ileal conduit / neobladder reconstruction / other) will be documented as well as whether there is a conversion to open surgery, and the reason for conversion. Total time of surgery as well as time taken for lymphadenectomy and urinary diversion (minutes) will be measured, in addition to milliliters of peri-operative bleeding. We will record multiple peri-operative data including nerve sparing (no / unilateral / bilateral), lymphadenectomy (not performed / bilateral external iliac nodes / bilateral presacral iliac), pelvic lymph node dissection (no / limited / standard / extended), partial prostatectomy, urethrectomy, and whether frozen section ureters (no / yes normal / CIS left / CIS right) or other frozen sections (no / normal urethra / CIS urethra / normal bundle) are performed.**Post-operative and histology data.** Post-operative staging and grading of tumors and CIS, as well as tumor histology (transitional cell carcinoma (TCC), adenocarcinoma, or other) and Gleason score [30] will be recorded. Post-operative pelvic node (total number and position) will be measured as well as the presence of prostate cancer in men. Positive margins for bladder and prostate will be measured. Number of days in hospital and readmission within 30 days post-surgery will be recoded.**Immediate (< 30 days) and late (30–90 days) post-operative complications.** In the event of a patient experiencing post-operative complications, the following characteristics will be recorded: number of complication events, time of first complication event, a description of each complication, Clavien-Dindo classification of immediate complications [31], and the date and description of treatment used. This information will be recorded both for immediate (30 days after surgery) and late (30–90 days after surgery) post-operative complications.**Follow up and outcomes.** All patients will be followed for 24 months after surgical intervention to assess multiple outcomes: mortality, tumor recurrence, continence, and sexual potency. In the event of a patient moving to another medical facility for follow-up treatment, the physician will be responsible for collecting follow-up data from them, with the patient’s consent. Follow-up data will include hospital readmission within 90 days, reoperation within 90 days, and mortality (and cause of death and autopsy data). In the event of tumor recurrence, data will be taken on date and localization of tumor recurrence, and subsequent treatment (adjuvant chemotherapy or radiation). Functional outcomes will include daytime and nighttime continence and sexual potency rates (at > 6 months and > 12 months) reported by patients to the physicians.

### Statistical analysis

Data will be cleaned and checked for discrepancies by a statistician before analysis. In cases of missing data, the responsible physician will be contacted and requested to check medical records and data-sheets for missing information. Characteristics of patients with missing data will be examined, and if necessary, sensitivity analysis or multiple imputation will be used to examine the effect of missing data on the results. Chi-square and students t-test will be used to assess differences in categorical and numerical data, respectively. The four main long-term outcomes of interest are recurrence-free survival, cancer-specific survival, overall survival, and functioning (continence and potency). Cox proportional regression models with 95% confidence intervals will be used to assess the risk of mortality or tumor recurrence according to the surgical technique used (open, laparoscopic, robot-assisted technique for cystectomy and/or urinary diversion). The exposure variable will be classified into different categories to also examine changes in surgery type during the operation (e.g., robot-assisted cystectomy and open surgery urinary diversion versus robot-assisted for both stages of the intervention). Logistic regression models, with adjustment for follow-up time, will be used to assess outcomes at different time points including: i) peri-operative factors (e.g., surgery time, blood loss, etc); ii) immediate post-operative factors (number of days in hospital post-operative complications etc) and; iii) long-term oncological and functional outcomes (mortality, tumor recurrence, continence and potency) up to 24 months post-surgery. Multivariable models will be used, with potential confounders selected both a-priori and on the basis of meeting the three statistical criteria for confounding (associated with the exposure, associated with the outcome, and not being on the causal pathway between exposure and outcome). Stratification and adjustment will be made according to the medical center, primary surgeon responsible for the operation and their years of medical experience, and various pre-surgery factors (tumor grading and staging, comorbidity, ASA score etc). Sample size is estimated according to a similar previous protocol [32], which is based on an overall complication percentage of 65% in the open radical cystectomy [33] with power set at 80% and alpha 5%, a sample size of 338 (2 × 169) patients is required to detect a decrease in the overall complication rate of 15%, i.e. from 65 to 50%.

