### Strengths and relevance

Despite the lack of randomization, there are several advantages of the current protocol. The current literature is largely based on non-randomized, retrospective analysis of clinical data, but our protocol was designed prospectively and will include a much larger sample size than the currently available studies. The multicenter design also provides some variation to the data, with 28 clinics all across Italy providing data, thus minimizing selection bias. Multiple surgeons in multiple clinics will perform the different surgical techniques on diverse groups of patients (different regions of the country, socioeconomic groups, rural and urban population etc), which will increase generalizability of the results. Though most studies compare two surgical techniques, we will compare three types (open, laparoscopic, and robot-assisted). Another novel aspect is that we will perform analysis that accounts also for change in technique during surgery (e.g., robotic-assisted cystectomy plus open urinary diversion surgery versus robotic-assisted surgery for both parts of the operation). Importantly, we have planned a long follow-up of 24 months that will allow us to examine both the short- and long-term outcomes in patients. A large proportion of the current evidence focuses on short-term outcomes and data is sparse on patients’ functional outcomes such as continence and potency, but we have included up to two-years of follow-up on multiple factors, including survival, functioning, and oncological outcomes, thus providing a more comprehensive picture.

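### Exposure is defined by the technique used and by changes during surgery, without separating planned hybrids from unplanned conversions, which could favour minimally invasive surgery

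*Protocol article*

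**What the plan says.** All the relevant text is in the protocol article.

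- **Statistical analysis.** The Cox models for mortality and recurrence compare patients "according to the surgical technique used (open, laparoscopic, robot-assisted technique for cystectomy and/or urinary diversion"). The next sentence reads: "The exposure variable will be classified into different categories to also examine changes in surgery type during the operation". Its one example is "robot-assisted cystectomy and open surgery urinary diversion versus robot-assisted for both stages of the intervention".
- **Variables (peri-operative data).** "Data on the surgical procedure will be categorized according to the technique used for cystectomy", and likewise for urinary diversion, with three options at each stage. The form also records "whether there is a conversion to open surgery, and the reason for conversion".
- **Phase II.** "Surgical technique will not be randomized and will be assigned according to the clinical judgement of the surgeon".
- **Strengths and relevance.** The approach is presented as a novel feature: "we will perform analysis that accounts also for change in technique during surgery". The example is again robotic cystectomy with open diversion.

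No section names the technique planned at the start of the operation as the exposure, lists planned technique as a data item, or says to which exposure group a converted patient belongs.

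**The concern.** The registry exists to compare three techniques. The surgeon's choice comes first and conversion can only follow it, during the operation. If conversion helps define the group, exposure depends partly on an early result of the exposure. The plan's own rule for confounders excludes variables on the causal pathway from technique to outcome. Conversion lies on that pathway, yet it may enter through the exposure variable instead.

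The wording covers two different things:

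- **A planned hybrid**, for example robotic cystectomy with a diversion intended from the outset to be open. This is fixed before surgery and is a legitimate exposure category.
- **An unplanned conversion.** This is an intra-operative event and belongs among the outcomes.

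Blood loss and operating time are themselves outcomes in this plan. If heavy bleeding or a long operation leads to conversion, a patient could leave the robotic or laparoscopic group because of the outcome being compared. The same mechanism could carry over to complications, length of stay and survival. The planned adjustment covers centre, surgeon and experience, and pre-surgery factors. It may reduce the distortion where these factors predict conversion, but it cannot be relied on to remove an effect created during the operation.

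**Working it through.** **1. The plan's own figure.** The sample-size paragraph starts from an "overall complication percentage of 65% in the open radical cystectomy" and seeks a fall to 50%, with 80% power and alpha 5%. Taking alpha as two-sided, with pooled variance under the null:

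n per group = [1.960·√(2·0.575·0.425) + 0.842·√(0.65·0.35 + 0.50·0.50)]² / 0.15² ≈ 169.3

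This agrees with the stated 169 per group (338 in total), and power at 169 per group is 79.9%. The figure does not depend on how conversions are classified. It is used here only to give a scale: the design difference is 15 points.

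**2. Set-up for the illustration.** Suppose there is no true difference by planned technique. Let p be the complication risk in both planned groups, c the proportion of the minimally invasive group that is converted, and q the risk in converted patients. The two planned groups are equal in size.

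- Unconverted minimally invasive: (p − c·q)/(1 − c)
- Open, if conversions are added to it: (p + c·q)/(1 + c)
- Open, if conversions form their own category: p

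The spurious difference (open minus minimally invasive) is therefore c(q − p)/(1 − c) with a separate category, and 2c(q − p)/(1 − c²) if conversions count as open.

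**3. Inputs.** None of c, q or the 60% base risk is in the article; all three are assumptions. The values are p = 60%, c = 5% or 10%, and q = 80% or 90%.

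| c | q | Unconverted minimally invasive | Open + conversions | Difference, own category | Difference, counted as open |
|---|---|---|---|---|---|
| 5% | 80% | 0.560/0.95 = 58.9% | 0.640/1.05 = 61.0% | 1.1 points | 2.0 points |
| 5% | 90% | 0.555/0.95 = 58.4% | 0.645/1.05 = 61.4% | 1.6 points | 3.0 points |
| 10% | 80% | 0.520/0.90 = 57.8% | 0.680/1.10 = 61.8% | 2.2 points | 4.0 points |
| 10% | 90% | 0.510/0.90 = 56.7% | 0.690/1.10 = 62.7% | 3.3 points | 6.1 points |

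Against the 15-point design difference, this is about 7–22% with a separate category (1.1/15 to 3.3/15) and 13–40% if counted as open (2.0/15 to 6.1/15).

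**4. Sensitivity.**

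- If q = p, both differences are zero. If converted patients did better than average, the sign would reverse.
- With the article's 65% as base risk, 10% conversion and 85% risk in converted patients give 2.2 points (own category) or 4.0 points (counted as open). A wider assumed range, 2–15% conversion and 65–95% risk, runs from 0 to 5.3 points or from 0 to 9.2 points respectively.
- The own-category result does not depend on group sizes. The counted-as-open result does: it is larger if the open group is smaller than the minimally invasive group, and smaller if the open group is larger.

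Analysed by planned technique, the difference is zero in every row.

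**The case against.** A reader might infer that the plan moves converted patients into the open group, or at least out of the minimally invasive groups, and so has a bias built in. The article does not support that.

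- **No rule is stated.** No section assigns conversions to any group. The form has a technique field for each stage and a separate conversion item. That layout would also fit coding a patient as robotic with conversion marked yes, which would keep the patient in the starting group.
- **The only example is a combination by stage.** Robotic cystectomy with open diversion may well be planned. Neither place that gives it mentions conversion.
- **The changes are to be examined as an addition.** The word also in the sentence suggests a supplement to the main comparison.
- **The figures rest on assumed inputs.** The larger ones require conversions to be counted as open. The separate category that the sentence suggests gives roughly half.
- **Pre-operative adjustment may help.** Stage, comorbidity and ASA score could partly predict conversion.

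All of this stands, and it limits the claim to a conditional one. It could further be said that an article may leave the handling of conversions to a fuller document. That does not dispose of the point. The article itself states that changes during the operation will help classify the exposure and counts this as a strength, and the comparison to which the changes are added is also by technique used. The rule as worded takes in unplanned conversions together with planned hybrids.

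**Conclusion.** The point holds in a conditional form. The plan defines exposure by technique used and by changes made during surgery, and does not distinguish a baseline choice from an intra-operative consequence. If conversions leave the group in which surgery began, and if converted patients do worse than average, the comparison is tilted towards minimally invasive surgery. Whether conversions go to a mixed category or to open changes the size of this, not its direction.

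The size cannot be established from the article. Under the main set of assumptions above it is small to moderate beside the design difference, and it disappears if converted patients carry average risk. Effects on blood loss, operating time, stay and survival follow the same logic but were not calculated. It would be too strong to say that the plan certainly biases the results, or that adjustment can do nothing about it. The wording should still be changed, because the remedy is cheap and standard.

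**What to change.** In the Statistical analysis section:

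1. Define exposure in the main analysis as the technique planned at the start of the operation, separately for cystectomy and for diversion. Planned hybrids then form their own baseline category.
2. Keep unplanned conversions in their planned group.
3. Report conversion, with its reason, as an outcome.
4. Keep the as-performed classification as a secondary analysis, labelled as such.

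Amend the statement under Strengths and relevance to match.

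Planned technique can be taken from the conversion item and its reason, together with operative notes for converted and mixed-technique cases. The item alone may not be enough. If technique was coded as finally performed, it would not show whether a converted case began robotically or laparoscopically, and no listed field separates a planned open diversion from an unplanned one. The recruitment window closed on 31 October 2020, before the article was published, so for most patients this will have to be reconstructed from records.

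The cost is that record check and the change of wording. The sample size does not change, and no new patients or procedures are needed.
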